*Outcome measures:* Patients' mental health status, daily functioning, and economic status will be measured at baseline, eight weeks and four months using three clinician administered rating scales: the General Health Questionnaire (GHQ-12), the World Health Organization Disability Assessment Scale (WHO-DAS 2.0 Brief), and a brief economic questionnaire. Qualitative semi-structured interviews will be used to understand the meaning that users, families and providers ascribe to any statistical associations found in the quantitative analyses, and to provide rich descriptions of experiences and perceptions of the program.

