*Analysis:* All participating patients will be included in the analysis. Patients who do not return for follow up will not be re-interviewed but will be included in final data analysis and we will examine baseline differences among those who do and do not complete follow-up interviews. Among patients who receive a score of  $> 2$  on the WHO DAS-II (indicating non-zero baseline disability) and a score of  $\geq 3$  on the GHQ-12 (indicating psychiatric caseness), we will calculate the percent of patients who experience clinically significant reductions in score (25% for the GHQ-12 and 20% for WHO-DAS-II Brief). Since there is currently no information on the percentage of individuals anticipated to achieve these score reductions within our population, we will assume this to be 50% (the most statistically conservative for sample size calculations – we expect this percentage to be greater which will increase our precisions). A sample size of 96 patients will allow us to estimate these proportions and 95% confidence intervals with precision of  $\pm 10$ . Assuming a drop-out rate of 20%, the minimum sample size for enrollment in the study will be 116. In order to stratify outcomes by characteristics such as age, gender, health center, diagnosis, and whether the patient is newly diagnosed or has previously been treated for a mental disorder, we will enroll as many patients are willing to participate (an estimate of 300 patients). We will use multivariable logistic regression to identify covariates associated with improved scores. Among individuals with low GHQ-12 and WHO-DAS-II Brief scores we will calculate within-person mean score change at eight weeks and four months. We will also calculate the percentage of patients who report improvements on the economic questionnaire and calculate mean score changes for individual responses.

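### The baseline cut-offs for GHQ-12 and WHO-DAS are joined by "and", so read literally patients high on one scale only have no primary-scale analysis, and on any reading mean change is planned only for low scorers

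*Protocol*

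**What the plan says.** All of the relevant text is in the Protocol, mostly in the Analysis paragraph of the quantitative outcomes evaluation.

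- The paragraph opens: "All participating patients will be included in the analysis".
- The set for percent improved is patients scoring above 2 "on the WHO DAS-II (indicating non-zero baseline disability) and a score of" at least 3 on the GHQ-12. Within that set the plan reports the percentage with "clinically significant reductions in score (25% for the GHQ-12 and 20% for WHO-DAS-II Brief").
- Mean change on the two scales is given one sentence: "Among individuals with low GHQ-12 and WHO-DAS-II Brief scores we will calculate within-person mean score change at eight weeks and four months". No cut-off for a low score is stated.
- The regression sentence names no analysis set: "We will use multivariable logistic regression to identify covariates associated with improved scores".
- The economic analysis carries no restriction on baseline score: "We will also calculate the percentage of patients who report improvements on the economic questionnaire and calculate mean score changes for individual responses".

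The data collection text of the same section makes mental health status (GHQ-12) and daily functioning (WHO-DAS Brief) the primary outcomes. The Executive Summary sets the visits: "Patients' mental health status, daily functioning, and economic status will be measured at baseline, eight weeks and four months". Aim 3 asks whether patients cared for at the selected health centers improve clinically and functionally, including economically.

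**The concern.** Two sets are defined for the primary scales: high on both, and low on both. Together they do not cover the cohort. A patient with disability but a GHQ-12 below 3, or the reverse, is in neither. That sits badly with the promise to analyse everyone.

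The program covers schizophrenia, bipolar disorder, major depression and epilepsy. A patient with epilepsy who is disabled but reports little psychological distress is a plausible member of the omitted group. If that patient's functioning improved, the percent-improved figure as written would not count it.

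A second problem does not depend on how the word "and" is read. Mean change on GHQ-12 and WHO-DAS is confined to those who start low and so have the least room to improve. A responder percentage among high scorers and a mean change among low scorers cannot be combined into one estimate of how much patients changed, which is what Aim 3 asks.

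**Working it through.** **1. The plan's own sample size.** Inputs from the Analysis paragraph: p = 0.5, half-width 0.10, 95% confidence.

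n = 1.96² × 0.5 × 0.5 / 0.10² = 96.04, so the stated 96 reproduces. The stated 116 is 96 × 1.2 = 115.2, rounded up. (Dividing by 0.8 would give 120. That is a separate matter, and nothing below depends on it.) The calculation allows for dropout but not for the share of enrolled patients who meet the baseline cut-offs.

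**2. Who is analysed on the primary scales, under each reading.**

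| Baseline status | Joint reading (literal) | Per-scale reading |
|---|---|---|
| High on both | Percent improved, both scales | Percent improved, both scales |
| High on WHO-DAS only | None | WHO-DAS percent improved; GHQ-12 mean change |
| High on GHQ-12 only | None | GHQ-12 percent improved; WHO-DAS mean change |
| Low on both | Mean change, both scales | Mean change, both scales |

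In neither column does a high scorer receive a mean change on the scale on which they are high, and neither column has a mean change for the whole cohort.

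**3. Size of the gap under the joint reading.** The Protocol gives no baseline distribution and no correlation between the scales, so these inputs are assumptions: proportion above the GHQ-12 cut-off a = 0.60, 0.70, 0.80; proportion above the WHO-DAS cut-off b = 0.80, 0.90, 0.95; latent bivariate-normal correlation r = 0.3, 0.5, 0.7. Let P be the probability of being high on both.

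Share high on one scale only = a + b − 2P

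- Smallest in the grid: a = 0.80, b = 0.90, r = 0.7. P = 0.769, so 1.70 − 1.538 = 0.162, or 49 of 300.
- Middle case: a = 0.70, b = 0.80, r = 0.5. P = 0.615, so 1.50 − 1.230 = 0.270, or 81 of 300.
- Largest: a = 0.60, b = 0.95, r = 0.3. P = 0.582, so 1.55 − 1.165 = 0.385, or 116 of 300.

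The range is about 16-39%, or 49-116 of the roughly 300 patients expected. Under the per-scale reading it is zero.

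**4. Consequence for precision under the joint reading.** Over the same grid P runs from 0.51 to 0.79. Half-width = 1.96 × √(0.25/m), with m = enrolled × 0.8 × P.

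- With 116 enrolled, m is about 48 to 73 and the half-width about 14 to 11.5 points, against the planned 10.
- With 300 enrolled, m = 240 × P is about 123 to 189 and the half-width about 8.8 to 7.1 points. The expected enrolment absorbs the restriction; the stated minimum does not.

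**The case against.** The strongest reply is that the paragraph is compressed rather than wrong. Each scale has its own cut-off, its own rationale and its own reduction threshold, and the sample-size sentence speaks of proportions in the plural. It is natural to read it as GHQ-12 response among GHQ-12 cases, WHO-DAS response among those with disability, and mean change for those low on the scale in question. The all-patients sentence supports that reading as much as it contradicts the other. This stands in part: the per-scale reading is plausible, and on it nobody is left out. But no sentence states it, and the literal conjunction appears twice, once for each set. Two analysts could draw different primary-outcome populations from this text.

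A reader might infer that patients high on one scale only enter no outcome analysis at all. The Protocol does not support that. Economic status is an outcome measure and part of Aim 3, and its analysis has no score restriction. These patients may also enter the logistic regression, whose set is unstated, and they belong in the baseline comparison of those who do and do not complete follow-up. What they lack, on the literal reading, is an analysis of change on GHQ-12 and WHO-DAS.

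A reader might also infer that the omitted patients will certainly concentrate in particular diagnoses. That is plausible given the case mix, but no figure in the Protocol shows it.

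Finally, responder proportions are a legitimate choice for the primary scales, the sample size is built on them, and model detail can be left to a statistical analysis plan. That is fair. The difficulty is that the Protocol itself fixes who receives a mean change, and fixes it to low scorers.

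**Conclusion.** The point holds in a limited form. As written, the cut-offs are joint, and patients high on one scale only have no planned analysis of change on either primary scale, in conflict with the all-patients statement. If the cut-offs were meant scale by scale, the defect there is one of wording and the number omitted is zero. On either reading, no average change on GHQ-12 or WHO-DAS is planned for the cohort that Aim 3 is about.

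The 16-39% range is conditional on the joint reading and on assumed proportions and correlation; the Protocol cannot confirm it. The confinement of mean change to low scorers rests on no assumption.

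This should be fixed before analysis. It does not invalidate the evaluation: the Protocol describes a single-group plausibility study, the scales are to be administered to all participants at baseline and to those who return at both follow-ups, and nothing is lost that a clearer analysis paragraph cannot recover.

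**What to change.** Rewrite the Analysis paragraph so that:

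1. GHQ-12 response (25% reduction) is reported among patients with baseline GHQ-12 of at least 3, and WHO-DAS response (20% reduction) among patients with baseline WHO-DAS above 2, each set defined without reference to the other scale.
2. Mean change on each scale at eight weeks and four months is estimated in all participants, for example with a repeated-measures mixed model per scale over the three visits.
3. The low-scorer mean change is kept as a subgroup description, with "low" defined as below that scale's cut-off.
4. The analysis set for the logistic regression is named.

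The cost is a few sentences and a standard model. No new data, visits or patients are needed.

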### ***Qualitative outcomes evaluation***

*Study Population/Recruitment:* A subset of patients recruited for the quantitative program evaluation will be purposively selected for the qualitative program evaluation. Approximately 40-50 “information rich” (e.g. willing and able to speak freely about their experiences) participants will be chosen by the clinician researcher or recommended by the health center nurse or the MESH mentor. The interviews will occur between October 2014 and July 2015. Selected

patients and their accompanying family member will be invited to participate in the semi-structured interview by the clinician researcher at the second or third follow up for the quantitative evaluation.

*Nurses:* All health center nurses (approximately eight nurses) participating in the MESH MH program at the four selected health centers will be invited to participate in the qualitative program evaluation by the trained clinician researcher or the PI. The nurses will be invited sequentially to participate during the nine month period (October 2014 to May 2015) following the initiation of the MESH MH program.

*Data Collection and Measurement:* Demographic data of participants will be obtained. Semi-structured interviews will be conducted by the mental health clinician researcher who will be trained and supervised by the PIs. The interviews will be conducted in Kinyarwanda and audiotaped, and the interviewer will take notes for context and non-verbal communication. The interview guide will be developed through an emergent design including insights gained from the investigator's experience working as a psychiatrist in Burera district for two years, as well as insights from other mental health workers in Rwanda and the literature on primary care integration models for mental health.

The semi-structured interviews will include sections to discuss access to and uptake of care, quality of care and outcomes for patients of the MESH MH program, as well as the health center nurse as an agent of delivery and overall experiences of the MESH mentorship model of care, including perceived needs for improvement. Interview guides will be tailored to the nurses, users and families, probing for experiences and opinions in each section. Interviews will be translated into English and transcribed for analysis.

*Data Analysis:* A content analysis will be conducted. Each transcript will be analyzed and coded for the themes of access to and quality of mental health care at the health center level, the health center nurse as an agent of delivery and the mentorship model of mental health care. Illustrative examples of any associations found in the quantitative outcome evaluation will also be identified and synthesized.

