### *Ethical issues:*

1. As this program evaluation occurs within the course of service provision for patients with mental disorders, one ethical challenge will be mitigating any fear that non-participation in the study will impact the services received by patients at the health center. This fear will be mitigated by strong emphasis in the informed consent process on how participation or non-participation will not affect patient's ability to obtain services at the health center. In addition, the research assistant will be charged with obtaining informed consent, to reduce any sense of coercion to participate that may arise if the patient's direct health care provider were responsible for obtaining consent.
2. Although the study takes place entirely within the context of service provision at health centers, some participating patients (e.g. patients without mutuelle) may find the follow up visits prohibitively expensive. If the research assistant becomes aware of participating patients who may qualify for transport and/or mutuelle assistance as specified in IMB MH program objectives, he/she will refer the patient to the Program Manager for Mental Health at IMB for further social assistance.

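### Patients for the Aim 4 interviews may be nominated by the nurse or mentor whose work the interviews assess, and nothing asks for patients who did not improve

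*Protocol*

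**What the plan says.** The Qualitative outcomes evaluation section (Study Population/Recruitment) defines the frame: "A subset of patients recruited for the quantitative program evaluation will be purposively selected for the qualitative program evaluation". About 40 to 50 participants are planned, to be "chosen by the clinician researcher or recommended by the health center nurse or the MESH mentor". The only stated criterion is being information rich, explained by the example "willing and able to speak freely about their experiences". The invitation is made "by the clinician researcher at the second or third follow up for the quantitative evaluation", and a clinician researcher also conducts the interviews.

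The topics listed in that section are access and uptake, quality of care, patient outcomes, the nurse as the person delivering care, the mentorship model, and what needs improving. The Data Analysis paragraph that follows codes transcripts for access, quality, the nurse and the mentorship model. It also looks for examples that illustrate associations found in the quantitative part. The Executive Summary (Outcome measures) gives the matching purpose: "to understand the meaning that users, families and providers ascribe to any statistical associations found in the quantitative analyses".

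Nurses are handled differently: all of them at the four centers, about eight, are invited. Under Ethical issues, the research assistant and not the care provider takes consent, "to reduce any sense of coercion to participate that may arise if the patient's direct health care provider were responsible for obtaining consent".

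**The concern.** Purposive sampling is a sound choice for this work. The difficulty is who may do the choosing. A nurse asked to suggest patients who will talk about her care, or a mentor asked to suggest patients who will talk about a service he supervises, may put forward those with whom things went well, without any intent to mislead. Nothing in the selection rule pulls the other way.

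Two things are at stake. The patient and family accounts under Aim 4 could read as more satisfied than the enrolled group is. And if few or no interviewees failed to improve, the interviews would have little to say about why some patients did not respond, which is part of explaining an association with improvement. The Dissemination section says that quantitative and qualitative data together will inform understanding of the program, and that scale-up recommendations follow if results are positive.

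**Working it through.** The plan gives no figure on this point to reproduce. The check is mainly a comparison of sections.

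1. **Nominators against topics.** The nominating roles are the clinician researcher, the health center nurse and the MESH mentor. The assessed subjects include the nurse's delivery of care and the mentorship model. Two of the three roles appear on both sides. Aim 2 and the supervision checklists confirm that nurse performance under mentoring is itself under evaluation.

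2. **Limits on nomination.** The two routes are joined by *or*, with no cap, no split and no record of source. The number of staff-nominated patients can lie anywhere from 0 to the full 40 to 50.

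3. **Variation by outcome.** The quantitative Analysis paragraph uses logistic regression to find covariates of improved scores. Such an association is a contrast between patients who improved and patients who did not, so interviews meant to illuminate it need some of each. The recruitment text neither requires nor excludes patients who did not improve.

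4. **Safeguards elsewhere.** The Executive Summary and the consent text for patients repeat the information-rich rule and add nothing on who selects. Consent by the research assistant protects against coercion and does not affect who is put forward. Limitations names the lack of a control group and the single, well-supported district, but not this selection.

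5. **Restriction to patients who return.** Invitation takes place at a quantitative follow-up visit, and "Patients who do not return for follow up will not be re-interviewed but will be included in final data analysis". This limit comes from the timing of the invitation. It would be the same whoever nominated.

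6. **Room for selection (illustrative).** Inputs from the quantitative Analysis paragraph: expected enrolment 300, minimum enrolment 116, assumed drop-out 20%. Share of retained patients needed to fill k places = k / [N × (1 − 0.20)].
   - N = 300: 300 × 0.80 = 240 retained; 40/240 = 17% and 50/240 = 21%.
   - N = 116: 116 × 0.80 = 92.8 retained; 40/92.8 = 43% and 50/92.8 = 54%.

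   At the expected enrolment, every place could go to a favourable patient even if only about one retained patient in five were favourable. At the minimum enrolment, roughly half would have to be. This shows how much room there is, not how likely such a sample is.

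7. **Timing of invitations.** Assessments are at baseline, eight weeks and four months, so the second or third contact is most naturally read as eight weeks or four months. The consent text supports this: enrolment from October 2014 plus eight weeks gives December 2014, the month in which qualitative consent opens. Enrolment to January 2015 plus four months gives about May 2015, inside the interview window that runs to July 2015.

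**The case against.** Asking key informants to name information-rich cases is a recognised form of purposive sampling, and nurses do know who will talk. Nomination is only one of two routes, the clinician researcher issues every invitation, and the guide asks about needed improvements. Aim 4 is exploratory. The Executive Summary lists uptake, quality of care and clinical outcomes as the evidence required before scale-up, not patient perspectives. All of this stands. It limits the weight of the point, but it does not alter the fact that assessed staff may select patients with no counterweight.

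Some stronger readings are tempting, and the documents do not support them.

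- A reader might infer that nomination fills the sample with patients who stayed in care. That restriction comes from inviting at follow-up visits.
- A reader might take the plan's 50% and expect 20 to 25 of the 40 to 50 interviewees not to have improved. The plan adopts 50% for lack of information, as the conservative value for precision, expects it to be exceeded, and applies it only above the baseline thresholds. The Executive Summary also counts about fifty patient and family participants together, so 40 to 50 may not all be patients.
- A reader might see a contradiction with the consent rule. That rule addresses coercion, a different aim from control of selection, so the two provisions can coexist.
- A reader might want a full quota on eight-week improvement. The plan defines significant reduction separately on two scales and only above baseline thresholds, so low scorers and patients with discordant scales would have no place. Such a quota would also push invitations towards four months and lose patients who drop out in between. The PI checks questionnaires only periodically, and the investigator's own work as a psychiatrist in the district means that PI selection is not wholly disinterested either.

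**Conclusion.** The point holds as a modest, avoidable weakness in the patient and family part of Aim 4. The recruitment rule allows staff to nominate patients for interviews about those staff's own work, asks for no variation by outcome, and is not acknowledged in Limitations. It permits a favourable sample; it does not make one certain, and it does not exclude patients who did not improve. The size cannot be stated beyond the range of none to all of the patient places. The nurse interviews and the primary outcomes are unaffected.

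This rests on two assumptions: that a recommendation can lead to inclusion without further screening, since none is described, and that the second or third follow-up means the eight-week or four-month visit. The first is the one that matters. If the clinician researcher in practice screens nominations against the whole list, the concern shrinks to recording the source of each selection.

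**What to change.** - In Study Population/Recruitment, delete the part of the sentence that lets the health center nurse or the MESH mentor recommend participants. Have the clinician researcher select purposively from the list of baseline participants already kept under Follow up, aiming for a spread across health center and diagnosis.
- For invitations at the four-month visit, allow the PI to add some patients who were above the baseline thresholds and reached the planned reduction on neither scale at eight weeks (25% for the GHQ-12, 20% for the WHO-DAS). Do not show the scores to the interviewer, so that the masking to previous questionnaires is kept.
- Keep invitations open at eight weeks, so that patients lost later are not excluded.
- State in Limitations that patients who do not return cannot be interviewed.

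The cost is a wording change, one sentence in Limitations and, for the PI's additions, scoring the eight-week questionnaires in time for the four-month visit. No extra staff or visits are needed. The downside is losing the nurse's and mentor's knowledge of who speaks freely. It is small, because the clinician researcher administers the study questionnaires and will normally have met each patient by then.

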### ***Quantitative outcomes evaluation:***

*Study Population/Recruitment:* All consecutive adults presenting to the mental health clinics at the four selected health centers for an initial visit between approximately October 2014 and January 2015, who have been diagnosed with a major mental or neurologic disorder, will be invited to participate in the quantitative outcomes evaluation. The mental health clinic day occurs once weekly as designated by the health center schedule. On that day, the clinician researcher will be available at the health center for enrollment in the research evaluation. Patients will be informed by the health center nurse, the MESH mentor and/or the clinician researcher present at the clinic, that a research evaluation of the mental health program will be occurring. If patients agree, the trained mental health clinician researcher will explain the evaluation further to the patient and determine whether the patient is willing to participate. Additionally, patients with a mental disorder who arrive at the clinic on a non-designated mental health clinic day will also be informed of the program evaluation by the health center nurse, and will be invited to return to participate the following week on the day that the clinician researcher will be present. Written informed assent from the patient and consent from his/her designated proxy will be obtained before data collection begins.

*Data collection, measures and outcomes:* The primary outcomes will be mental health status and daily functioning, measured at first visit, eight weeks and four months after beginning participation in the MESH MH program. Outcome measures will be determined by two clinician administered scales: the General Health Questionnaire (GHQ-12) and the World Health Organization Disability Assessment Scale (WHO-DAS 2.0 Brief). These scales have demonstrated high levels of validity and reliability and have been used extensively in developing countries. A brief economic status questionnaire for patients with mental disorders, adapted from other resource limited contexts, will also be administered. All instruments will be translated into Kinyarwanda and back translated prior to implementation. The symptom and functioning scales will be used prior to the study by staff at the district mental health clinic and a small convenience sample of patients to ensure face validity.

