The three scales will be administered by the trained clinician researcher who will be available on the designated mental health clinic days for questionnaire administration. If the clinician researcher determines that a patient is unable to offer adequate answers to questions secondary to severe mental illness (e.g. the patient exhibits clinical signs of severe psychosis such as disorganized thinking), the primary family member in attendance at the clinic with the patient

will be used as a proxy to answer questions, and the fact that a proxy has been used will be recorded. Demographic information as well as self-reported treatment status (new to treatment or received previous treatment) will be recorded. The PI will periodically check all completed questionnaires to ensure data quality and re-interview a random selection of respondents to verify data reliability.

*Follow up:* The mental health clinician researcher will maintain a list of patients who participated in the baseline data collection. Patients will be re-interviewed at eight week and four month follow up, on their return for follow up to the health center. For patients who do not return to follow-up, a community health worker in their village will be contacted to visit the patient and encourage the patient to return to care (as is routine practice in the current health system). Patients who return will be re-interviewed at eight week and four month follow up. The interviewer will not have sight of the previous questionnaires on follow up interviews.

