### **Patients:**

*Quantitative Evaluation:* The initial consent process will occur at the four selected health centers following patients' routine appointments for a mental disorder between approximately October 2014 and January 2015. In cases where patients are potentially interested in participating as determined by the recruitment procedure, the research assistant will describe the quantitative evaluation process in some detail, including the purpose of the study, the anticipated benefits and risks, and voluntariness issues, to both the patient and his/her accompanying family member, and answer any questions which may arise. If the patient and family member then agree to participate, the research assistant will then obtain assent from the patient and consent from the accompanying family member

The research assistant will be charged with obtaining assent and consent from patients and their family members, to reduce any sense of coercion to participate that may arise if a direct health care provider were responsible for obtaining consent. A strong emphasis will also be placed on how participation or non-participation will not affect care provided at the health centers, in order to mitigate any fear that non-participation will impact services received by patients. Patients will be reminded throughout the study period that their participation is voluntary and continuing assent to continue will be ascertained verbally at both follow up study visits.

*Qualitative Evaluation:* The initial consent process for the qualitative evaluation will occur at the four selected health centers following patients' routine appointments for a mental disorder between approximately December 2014 and September 2015. Purposively selected "information rich" patients who have assented to the quantitative evaluation will be asked with their family members by the research assistant if they are both willing to participate in a qualitative evaluation consisting of the longer semi-structured interview. The research assistant will then describe the qualitative evaluation process in some detail, including the purpose, anticipated risks and benefits, voluntariness and confidentiality issues. If the patient and family member agree to participate, the research assistant will then obtain assent from the patient and consent from the accompanying family member.

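### The protocol lets the role that rates the primary scales hold a long interview covering outcomes before a patient's four-month rating, and its visit wording and dates do not agree

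*Protocol*

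**What the plan says.** **Who rates and who interviews.** Under Quantitative outcomes evaluation: "The three scales will be administered by the trained clinician researcher". Under Qualitative outcomes evaluation: "Semi-structured interviews will be conducted by the mental health clinician researcher who will be trained and supervised by the PIs". The same role may also choose the patients, who are picked because they talk readily about their experience. The health center nurse or the program mentor may recommend them too.

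**When.** Patients and accompanying relatives are "invited to participate in the semi-structured interview by the clinician researcher at the second or third follow up for the quantitative evaluation". The primary outcomes are "measured at first visit, eight weeks and four months after beginning participation in the MESH MH program", so there is one baseline and two follow-ups. The Patients section under Ethical Considerations confirms the count: "continuing assent to continue will be ascertained verbally at both follow up study visits".

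**Dates.** Quantitative enrolment runs from about October 2014 to January 2015. The qualitative section has interviews from October 2014 to July 2015. The Patients section has qualitative consent following "routine appointments for a mental disorder between approximately December 2014 and September 2015".

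**Masking.** The one rule is: "The interviewer will not have sight of the previous questionnaires on follow up interviews".

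**Content and length.** The interview covers access and uptake, quality of care, patient outcomes, the nurse's role, the mentorship model and what needs improving. Safety Considerations gives it 30-60 minutes, against 15-30 minutes for the scales.

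**The concern.** The study has no control group, so anything that moves the follow-up rating moves the reported percent improved. Hiding old questionnaires is meant to stop earlier information from shaping later ratings. If the rater has discussed a patient's outcomes and care at length at eight weeks, two things can carry into the four-month rating: the rater's expectation, and the patient's wish to stay consistent with the account already given.

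Exposure would not be random, because patients are chosen for their readiness to talk, by the rater or by staff close to the program. Where a relative answers the scales as proxy, that relative may be the one interviewed as well, so the respondent is exposed along with the rater.

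**Working it through.** **Step 1: which visit is meant.** There are three assessments (first visit, eight weeks, four months), and two of them are follow-ups.
- Counting follow-ups only, the second is four months and a third does not exist.
- Counting assessments from baseline, the second is eight weeks and the third is four months. Only this count gives both words a visit.

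**Step 2: dates.**
- Earliest enrolment, 1 October 2014: plus 8 weeks = 26 November 2014; plus 4 months = about 31 January 2015.
- Latest enrolment, 31 January 2015: plus 8 weeks = 28 March 2015; plus 4 months = about 2 June 2015.

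Consent opening in December 2014 fits the eight-week reading. Interviews opening in October 2014 fit neither reading, because no follow-up of any kind could have taken place. Interviews end in July 2015, while consent runs to September 2015.

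**Step 3: is there a sequencing rule?** No section places the interview after the four-month scales, sets the order of scales and interview within a visit, or requires an interviewer other than the rater.

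**Step 4: the plan's own precision.** n = 1.96² × 0.5 × 0.5 / 0.10² = 96.04, which matches the stated 96. The half-width at 96 is 10.0 points. With 300 enrolled and the stated 20% drop-out, completers = 300 × 0.8 = 240, and the half-width is 1.96 × √(0.25/240) = 6.3 points.

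**Step 5: size of a possible shift.** Shift in percent improved = (exposed patients / completers) × assumed effect on an exposed patient's chance of being scored improved. The documents give no such effect; 20 points is an assumption, with 10-30 as a range. The upper bound has all 40-50 participants as patients interviewed before their four-month rating. The lower pair assumes that half are relatives, since the Executive Summary counts about fifty patients and family members together.

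| Exposed patients | Completers | Exposed share | Shift at 20 points | Shift at 10-30 points | CI half-width |
|---|---|---|---|---|---|
| 40-50 | 240 | 16.7-20.8% | 3.3-4.2 | 1.7-6.3 | 6.3 |
| 40-50 | 96 | 41.7-52.1% | 8.3-10.4 | 4.2-15.6 | 10.0 |
| 20-25 | 240 | 8.3-10.4% | 1.7-2.1 | 0.8-3.1 | 6.3 |
| 20-25 | 96 | 20.8-26.0% | 4.2-5.2 | 2.1-7.8 | 10.0 |

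The shift may be up or down. If only half of the exposed patients are interviewed early, each figure halves. The improvement analysis is limited to patients above the baseline cut-offs, so the true shares depend on how many in each group pass them, which the protocol does not give.

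**The case against.** A reader might infer that the stated masking fails and that the four-month outcome is contaminated. The protocol does not support that.

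- **The rule holds as written.** It bars sight of earlier questionnaires, and a qualitative interview shows none.
- **Familiarity exists anyway.** The same role rates each patient at every visit and may remember earlier answers. The interview adds to that, by an amount nobody can state, and moving it leaves the rest in place.
- **Early interviews are permitted, not required.** The text fixes the invitation, not the interview date, and a shared role need not be one person. Read literally, the second follow-up is the four-month visit, with no later rating to affect.
- **Content and direction.** Outcomes are one topic among several. Criticism voiced to the rater could lower a later rating as easily as praise could raise it.
- **Other safeguards.** The principal investigator checks questionnaires and re-interviews a random selection, and the Limitations section restricts causal claims. The re-interviews test reliability, however, and do not mask the rater.
- **Design intent.** Study Design calls for simultaneous qualitative and quantitative evaluation, and late interviews lose the views of patients who drop out.

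All of this limits the strength of the finding. It does not remove the gap: the literal reading leaves the third follow-up without a visit, and no sentence rules out an outcomes interview by the rater before the four-month scales.

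**Conclusion.** The point holds as a gap in sequencing and a contradiction in wording, not as proof of bias. The protocol permits the rater's role to hold the interview from the eight-week visit onward, before the four-month primary rating. The visit count and the December consent date make that the more plausible reading, though the October interview start does not fit it. The purpose of the masking rule is undermined for a non-random subset of at most 40-50 patients.

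At an assumed 20-point effect the shift is modest at the expected enrolment, about 3-4 points and within the 6.3-point half-width. At the 96-completer minimum it is about 8-10 points and rivals the planned precision. Both roughly halve if only 20-25 are patients. These sizes rest on an effect that the documents do not supply and on every exposed patient being interviewed early. The direction is unknown.

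**What to change.** 1. Reconcile the visit wording and the interview dates in Qualitative outcomes evaluation with the two-follow-up schedule in Quantitative outcomes evaluation and the consent window in the Patients section.
2. State in Qualitative outcomes evaluation that the patient and family interview takes place only once that patient's four-month GHQ-12, WHO-DAS and economic questionnaire are complete.
3. If any interview is held at the eight-week visit, do it after that visit's scales, flag the patient, and report the four-month result with and without flagged patients.

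**Cost.** A few sentences and no extra staff. The last four-month visit falls at about the start of June 2015, which leaves roughly two months of the interview window to July. Interviews start about two months later than the eight-week reading allows. Patients lost between eight weeks and four months are not interviewed unless the flagged early route in item 3 is used.
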